# Effectiveness of expiratory technique and induced sputum in obtaining good quality sputum from patients acutely hospitalized with suspected lower respiratory tract infection: a statistical analysis plan for a randomized controlled trial

**DOI:** 10.1186/s13063-021-05639-1

**Published:** 2021-10-02

**Keywords:** Randomized controlled trial, Statistical analysis plan, Sputum sample, Tracheal suction, Forced expiratory technique, Induced sputum, Respiratory tract infection

## Abstract

**Background:**

Targeted antimicrobial treatment is essential to avoid unnecessary use of broad-spectrum antibiotics and antimicrobial resistance. Targeted treatment relies on a precise microbiological diagnosis — in pneumonia, this poses a challenge as the usefulness of Gram stains and cultures is highly dependent on the quality of the sputum sample.

This study aims to examine adverse effects and quality of sputum samples obtained by expiratory techniques (forced expiratory technique and sputum induction) compared with tracheal suction. The hypothesis is that expiratory techniques are non-inferior to tracheal suction in obtaining samples from the lower respiratory tract. This statistical analysis plan (SAP) describes the study design, method, and data analysis of the trial to increase transparency, avoid reporting bias or data-driven analysis and increase the study’s reproducibility.

**Method:**

The design is a pragmatic, non-inferiority, parallel-arm randomized controlled trial including 280 patients admitted with suspected lower respiratory infection to two emergency departments. Patients are randomized to a usual care group, where sputum samples are collected by tracheal suction or to an intervention group where sputum samples are collected by forced expiratory technique and sputum induction. The statistical analysis will follow an intention-to-treat protocol. This SAP is developed and submitted before the end of recruitment, database closure, and statistical analyses.

**Discussion:**

The results of this study will provide valuable knowledge to clinical practice by comparing adverse effects and sputum sample quality associated with different sample methods.

**Trial registration:**

Clinicaltrials.gov, NCT04595526. Submitted on October 19, 2020

**Supplementary Information:**

The online version contains supplementary material available at 10.1186/s13063-021-05639-1.

## Administrative information {1}

Note: the numbers in curly brackets in this protocol refer to recommended guidelines for the content of a statistical analysis plan of a clinical trial developed by Gamble et al. [1] (Additional file 6). The protocol has been reported according to SPIRIT reporting guidelines [2].

## Background {7}

Lower respiratory tract infection (LRTI) is a serious condition associated with high mortality, morbidity and economic burden [3–5]. Appropriate and targeted antimicrobial treatment is vital to avoid unnecessary use of broad-spectrum antibiotics and subsequent development of bacterial resistance.

Sputum Gram stain and culture from patients with LRTI are important when selecting a targeted antimicrobial treatment [6, 7].

Several clinical limitations interfere with the practice of obtaining a representative specimen from the lower respiratory tract (LRT). Many patients find it difficult to expectorate, sputum is often contaminated by oropharyngeal microbiota, and some patients have already been treated with antibiotics at admission, compromising the results from sputum culture [8–10]. The guidelines from the American Thoracic Society and Infectious Diseases Society of America recognize the challenges in obtaining a valid sputum sample. They recommend sputum analyses based on individual clinical assessment, local etiological considerations, and local antimicrobial stewardship [11].

The Danish guidelines [12] follow the National Institute for Health and Care Excellence guidelines [13] and are further developed by experts in the fields of microbiology, infectious disease, and emergency medicine. It is required that sputum samples must be collected at arrival at the emergency department (ED) from all patients admitted with suspected LRTI, and advocate tracheal suction as an optimal collecting method [12]. Despite indications from some studies that tracheal suction might be superior to expectorated sputa in diagnosing LRTI [14, 15], low accuracy and misclassification of poor samples have been reported [16, 17]. Tracheal suction is widely performed to clear pulmonary secretions in mechanically ventilated patients [18] but reported as a painful experience for the patient [19] being associated with adverse events such as hypoxia, oxygen desaturation, and mucosal bleeding [20]. Forced expiratory technique and sputum induction are considered safe and straightforward methods [21] and are used successfully to clear airways and increase sputum production, facilitating collection for microbiological analyses when patients are unable to expectorate [22–25].

The most effective method to collect a representative specimen from the LRT remains uncertain. The efficacy of tracheal suction, forced expiratory technique and sputum induction to obtain sputum samples of high quality has not been investigated in an ED context.

### Hypothesis, aim, and objectives {8 +12}

We hypothesize that expiratory techniques (forced expiratory technique and sputum induction) are non-inferior to tracheal suction in obtaining sputum samples from the lower respiratory tract.

This study aims to investigate the effectiveness of expiratory techniques compared to tracheal suction on the quality of sputum samples collected from patients acutely hospitalized with suspected LRTI.

The following objectives will be explored:
Is the proportion of suitable (good quality) sputum samples different when comparing samples obtained by tracheal suction to samples obtained by expiratory techniques?Is the number of adverse events different when comparing tracheal suction to expiratory techniques?How do patients experience the two sputum sample collecting procedures?

This statistical analysis plan (SAP) will describe the statistical analysis to be executed on primary and secondary outcomes to increase study transparency, reproducibility, and validity. This SAP was developed after the study protocol was registered with the following organizations: Danish ethics committee; clinical trials; data protection agency and, before database closure, data review; and commencement of any statistical analyses.

## Method

This SAP followed the recommended guidelines for a statistical analysis plan of a clinical trial developed by Gamble et al. [1]. A checklist for SPIRIT reporting guidelines and a template for the schedule of enrolment [2] is attached as Additional files 1 and 3. The study will follow the Consolidation Standard of Reporting Trials (CONSORT) guidelines (parallel-group randomized trials) [26].

### Study design and setting {9}

The study design is a pragmatic, non-inferiority, randomized controlled trial (RCT). The trial is conducted from the 9th of November 2020 until the 1st of July 2021 at the University Hospital of Southern Denmark including the hospitals of Aabenraa and Sønderborg with a hospital coverage of approximately 250,000 inhabitants. The standard method for sputum collection at both EDs is tracheal suction.

Six project assistants from the ED (experienced nurses and physiotherapist) will identify eligible patients and collect informed consent (Additional file 5) and data. The project assistants will receive bedside and simulation training in all the included sample methods on how to obtain an optimal specimen. Furthermore, a guideline on how to perform the expiratory technique will be developed to support consistent data collection.

### Trial population

#### *Screening data* {21}

Screenings data from previous studies was used to estimate the sample size of our trial population [9, 10, 23, 27, 28]. Use of this data ensures our results will be reproducible.

#### Eligibility {22}

Adults admitted to the ED with suspected LRTI will be invited to participate in the study if the attending physician identifies one of the following pulmonary symptoms: dyspnea, cough, expectoration, chest pain, or fever (Fig. 1).

**Fig. 1 Fig1:**
[figure not shown]
Recruitment procedure and allocation

Patients will be excluded if the following occur:
The attending physician finds that participation will delay urgent treatmentPatients are transferred to an intensive care unitPatients have severe immunodeficiencies such as human immunodeficiency virus infection (a CD4 count below 200/μl)Patients are treated with immunosuppressive therapy such as chemo- or radiotherapyPatients are treated with steroids in a prednisolone equivalent dosage of more than 20 mg/day for 2 weeks up to the current admission or if consent cannot be obtained

#### Recruitment {23}

Admitted patients with suspected LRTI will be identified in the patient management system (CETREA 4.2.0.0.) at the ED by a project assistant. The attending physician will confirm eligibility, and the patient’s verbal and written consent will be obtained by the project assistant within the first hour of admission.

### Randomization {10}

Within an hour after recruitment, enrolled patients are randomly assigned to either control (sputum collection by tracheal suction) or intervention (sputum collection by forced expiratory techniques). Patients in the intervention group who cannot deliver a specimen will undergo tracheal suction according to regional guidelines, and these samples will not be included in the primary analyses.

Patients are allocated 1:1 according to a computer-generated randomization sequence without stratification using blocks of six programmed by an independent data manager, so the treatment assignment is made by chance and the allocation is completely independent of any prior treatment allocation to a patient. The randomization tool in Research Electronic Data Capture (REDCap) will be used [29, 30]. The project assistants administering the randomization will not have access to the randomization code and will be blinded to the randomization procedure, block sizes, and randomization sequence at all times during the trial period. In addition, allocation concealment is ensured, as the randomization is performed electronically, is not revealed before consent is obtained, and occurs immediately prior to sputum collection.

#### Blinding

Participants, project assistants, and outcome adjudicators are not blinded to the randomization as it is not possible. The investigator will be blinded until data analysis is completed.

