### Microbiological variables

#### Microscopy

Part of the sputum is placed on a microscope slide with a cotton swab, and a second microscope slide is used to distribute the material on the surface. The smear is then heat-fixed and Gram stained. The number of squamous epithelial cells and polymorphonuclear leucocytes per field of view (100× magnification) is registered. Samples with < 10 squamous epithelial cells per field of view are classified as suitable (good quality), samples with ≥ 10 squamous epithelial cells are classified as unsuitable (poor quality) [32]. The microscopy findings and classification are registered in the microbiological laboratory information system (MADS, Aarhus University Hospital, Aarhus, Denmark) and are accessible in the patient’s file.

In addition, a different sputum quality assessment based on both squamous epithelial cells and polymorphonuclear leucocytes will be used in sub-analyses. Samples with < 10 squamous epithelial cells and ≥ 25 polymorphonuclear leucocytes per field of view (100× magnification) are classified as suitable (good quality) [32].

The samples unable to be collected will be considered missing as the quality cannot be determined.

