### Outcome definitions {26}

*Primary outcome*. The quality of sputum samples, binary outcome*Secondary outcome 1*. Number of adverse events, discrete outcome
Aggravation of SaO_2_ and SaO_2_ ≤ 93% (COPD patients ≤ 88%), binaryAggravation of RR and RR lower than 12 or higher than 20 times per minute, binaryOccurrence or aggravation of symptoms (cough, expectoration, dyspnea, chest pain), binaryAggravation of patient symptoms experience, binaryOccurrence of side effects observed by the project assistant, binaryDeath within 7 days from admission, binary30 days re-admission after current hospitalization, binary*Secondary outcome 2*. Patient experience of the sputum collection procedure, ordinal outcome

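### The plan declares outcome adjudicators unblindable without separating the primary outcome, a smear count read by microscopy, so an avoidable risk of detection bias stays in the only primary comparison

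*SAP article*

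**What the plan says.** The Blinding paragraph reads "Participants, project assistants, and outcome adjudicators are not blinded to the randomization as it is not possible", followed by "The investigator will be blinded until data analysis is completed". Nobody else is said to be blinded.

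Outcome definitions {26} gives the primary outcome as "The quality of sputum samples, binary outcome". The Microscopy section says how it is obtained. A smear is heat-fixed and Gram-stained, then "The number of squamous epithelial cells and polymorphonuclear leucocytes per field of view (100× magnification) is registered". The rule is "Samples with < 10 squamous epithelial cells per field of view are classified as suitable (good quality"), and 10 or more is unsuitable. Then: "The microscopy findings and classification are registered in the microbiological laboratory information system". The section on adjustments before study start adds that the criterion for every randomized patient is the microbiological department's own standard. The section on confidence intervals and p-values confirms that there is only one primary outcome.

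The plan does not define the outcome adjudicators. It does not mention coded specimens, withholding of the collection method, or a second reading. Data monitoring names an independent microbiologist with a data quality role but does not say that this person is masked.

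**The concern.** The stated reason suits outcomes recorded at the bedside: symptoms, saturation, respiratory rate, observed side effects, patient experience. It does not obviously suit a count made on a stained slide. The sentence makes no exception for the primary outcome, so as written it covers the one measurement on which the trial is decided.

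If the reader knows how the specimen was collected, that knowledge can affect how a count close to 10 is called. Any effect that differs between arms enters the outcome value itself. The planned mixed model, covariate adjustment and multiple imputation all take the recorded class as given, so none of them would correct it.

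**Working it through.** **Does the reason carry over?**

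| Group | Role | Does the procedure itself reveal the arm? |
|---|---|---|
| Patients | Undergo suction or the expiratory technique | Yes |
| Project assistants | Collect the specimen, record bedside outcomes | Yes |
| Smear reader | Counts cells on a Gram-stained smear | Not stated; only through label, request or specimen appearance |

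The Exposure variables section ends each of the three techniques with storage in a sterile container. It does not say that the containers are identical. Suction uses lubricating jelly, and the specimen may be diluted with saline. These features could give the method away in some cases, but they do not make it impossible to leave the method off the label and request.

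**The plan's own power figure, reproduced first.** Inputs from Sample size consideration {11}: 260 patients, good quality 90% (suction) and 75% (expiratory), no sample in 10% with suction, in 50% with forced expiration alone, and in 30% with induction added. Allocation is 1:1, so 130 per arm.

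- Suction: 130 × 0.90 = 117 samples.
- Expiratory, if induction follows failed forced expiration: missing 0.50 × 0.30 = 15%, so 130 × 0.85 = 110.5 samples.
- Standard error under the pooled proportion: SE0 = √[p̄(1−p̄)(1/117 + 1/110.5)], with p̄ = (105.3 + 82.875)/227.5 = 0.827, gives 0.0502.
- Unpooled: SE1 = √(0.9×0.1/117 + 0.75×0.25/110.5) = 0.0497.
- Power = Φ[(0.15 − 1.96×0.0502)/0.0497] = Φ(1.04) = 85.1%.

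Reading the 30% as missing in the whole expiratory arm (91 samples) gives 81.7%. The stated 84% lies between the two, so the sample counts below are consistent with the plan.

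**Illustration of a differential reading shift.** The documents give no size for reading error, so the shift s is an assumption. Suppose there is no true difference, both arms are at 75%, and reading moves the suction arm's observed proportion by s:

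P(reject) = Φ[(s − 1.96·SE0)/SE1] + Φ[(−s − 1.96·SE0)/SE1]

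| s | Samples (s × 117) | SE0 | SE1 | Two-sided error |
|---|---|---|---|---|
| 0 | 0 | 0.0574 | 0.0574 | 5.0% |
| 2 points | 2.3 | 0.0566 | 0.0567 | 6.5% |
| 5 points | 5.9 | 0.0553 | 0.0554 | 14.8% |

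With 91 expiratory samples the last two rows become 6.4% and 14.0%. Direction hardly matters for this measure: with 110.5 samples, moving the expiratory arm up instead gives 6.4% and 14.6%.

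**Non-inferiority scale.** If the 15 points that the plan calls clinically significant are taken as the margin (also an assumption), with a true deficit of exactly 15 points and a reading shift favouring the expiratory arm, false non-inferiority is Φ(s/SE1 − 1.96). That is 2.5% at s = 0, Φ(0.02/0.0487 − 1.96) = 6.1% at 2 points, and Φ(0.05/0.0471 − 1.96) = 18.5% at 5 points.

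**The case against.** The plan discloses the lack of blinding openly and keeps the investigator blinded until analysis is complete. The outcome is a number with a fixed cut under a routine departmental standard, which leaves little discretion except near 10. The trial is pragmatic, and an added laboratory technique had already been dropped because it needed staff training during the pandemic. Outcome adjudicators is an undefined term and may mean those who record adverse events. The request form is not described, so the effort of masking cannot be fully verified. All of this lowers the urgency. None of it supplies a reason why the smear reader could not be masked, and blinding the investigator does not protect the count.

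Four stronger readings are tempting, and the documents do not support them.

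- **That readers would favour suction** because it is the standard method at both departments. Nothing shows such a preference among laboratory staff, and the trial's hypothesis could as easily suggest the opposite lean.
- **That the plan admits reader error** where the Background says "low accuracy and misclassification of poor samples have been reported". In context, that sentence is about suction as a collection method, not about counting near the cut.
- **That the bias would be some 4.5 to 9 points.** Such a figure can be obtained by assuming lognormal counts with log-SD 1.0 to 2.0 and a 20% distortion of every count, in opposite directions in the two arms. None of these inputs is in the plan, so this is a worst case and not an expected size.
- **That no reason is given at all.** One is given, but it does not cover a smear reading.

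**Conclusion.** The point stands as a should-fix. The Blinding section extends to all outcome adjudicators a reason that fits only patients and project assistants. Nothing elsewhere in the plan states that the primary outcome is read without knowledge of the method. The result is an avoidable risk of detection bias in the only primary comparison. The bias is possible, not shown, and its size and direction are unknown.

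The rise in two-sided error from 5% to about 6.5% to 15% rests on an assumed shift of 2 to 5 points in one arm, on 110 to 117 evaluable samples per arm, and on a normal approximation. It shows that a few reclassified samples are enough to matter, not that they occurred. The conclusion also takes the smear reader to be among the adjudicators, which is the natural reading but is not stated. Sample size, alpha and stated power are unaffected.

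**What to change.** 1. Limit the statement that blinding is not possible to patients and project assistants, and state who reads and classifies the smears.
2. For specimens not yet read, send them to the laboratory under a trial number without the collection method or arm, and have the quality class entered before the method can be seen.
3. For smears already read openly, say so, report how many, and name it as a limitation. Recruitment began on 9 November 2020 and was planned to end in early July 2021, and the article appeared on 2 October 2021. A flat statement that readers are blinded would therefore misdescribe readings already made.
4. Optionally, if slides were kept, have them re-read by a masked reader and report the agreement.

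Items 1 and 3 cost only wording and a count. Item 2 needs a changed label and request text but no extra reader. Its drawbacks are that specimen appearance or saline dilution may unblind some readings, and that the laboratory does not see the method until the class is entered. Item 4 needs a masked reader's time and depends on slides having been retained, which the plan does not say.

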### Exposure variables

#### Tracheal suction

Before tracheal suction is performed, the patient will be informed in detail about the procedure. The patient is introduced to Fowler’s position (semi-sitting position in 45–60° with knees either bent or straight) and encouraged to clear their airway with a deep cough. The catheter (EXTRUDAN Surgery Aps, Denmark, CH12, 530 mm) tip is lubricated with Xylocaine (lidocaine HCl) 2% jelly and inserted into the nares during inhalation and gently advanced about 40 cm without applying suction. The suction catheter port is covered, and suctioning is performed before withdrawing the catheter. Suction is set at 200–400 mmHg negative pressure. If necessary, the specimen is diluted in sterile saline water before storage in a sterile container.

#### Sputum samples collected by forced expiratory techniques

These techniques are based on the patients’ own attempts to deliver a sputum sample. The patient is brought into a 90° sitting position and instructed to clear the mouth with water to minimize oropharyngeal contamination, and proper forced exhalation and the coughing technique are thoroughly explained [24, 31].

The patient takes 3 to 5 deep diaphragmatic breaths, inhaling through the nose, exhaling through pursed lips. The patient takes a normal breath and then squeezes it out by contracting the abdominal and chest wall muscles, with the mouth and glottis open, while whispering and forcing the word “huff” during exhalation. The procedure is repeated 3 to 5 times. As secretions enter the larger airways, the patient exhales from high-to-mid lung volume to clear secretions from more proximal airways. The procedure continues as the patient takes 3 to 5 relaxed diaphragmatic breaths before coughing again [24, 31]. The sputum sample is stored in a sterile container.

#### Induced sputum

Isotonic saline inhalation (0, 9%) is used to loosen and induce the sputum. It is given for 10 min with a nebulizer system (Unomedical Opti-Mist TM,2.1m, ref. 93-772mm) [22]. After that, a forced expiratory technique is performed, and the sputum sample is stored in a sterile container.

Inhalation medicine is permitted as part of concomitant care.

### Microbiological variables

#### Microscopy

Part of the sputum is placed on a microscope slide with a cotton swab, and a second microscope slide is used to distribute the material on the surface. The smear is then heat-fixed and Gram stained. The number of squamous epithelial cells and polymorphonuclear leucocytes per field of view (100× magnification) is registered. Samples with < 10 squamous epithelial cells per field of view are classified as suitable (good quality), samples with ≥ 10 squamous epithelial cells are classified as unsuitable (poor quality) [32]. The microscopy findings and classification are registered in the microbiological laboratory information system (MADS, Aarhus University Hospital, Aarhus, Denmark) and are accessible in the patient’s file.

In addition, a different sputum quality assessment based on both squamous epithelial cells and polymorphonuclear leucocytes will be used in sub-analyses. Samples with < 10 squamous epithelial cells and ≥ 25 polymorphonuclear leucocytes per field of view (100× magnification) are classified as suitable (good quality) [32].

The samples unable to be collected will be considered missing as the quality cannot be determined.

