### Harms {30}

The project includes collecting methods that are already applied and recommended in clinical practice. There are minimal indications of adverse effects of a spontaneous cough or induced sputum after inhaling an isotonic saline solution (0.9%) [21, 22]. It is known that the tracheal suction routine carries a risk of airway bleeding, although this is rare and often short-lived [20]. Moreover, there may be short-term discomfort, especially during the tracheal suction procedure [19]. Patients will be informed of the adverse events verbally and in writing. In case of an aggravation of symptoms, the procedure that is being performed will be interrupted preventing patient participation. The procedures are known to have minimal risks and the hospital will provide routine ancillary post-trial care, if necessary.

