#### Definition of analyses population {20}

The primary analysis will be conducted according to the intention-to-treat (ITT) principle [46, 47].

We define the ITT population as all admitted patients suspected of LRTI who sign informed consent and subsequently are allocate to one of two sputum collection groups. Sputum samples obtained by tracheal suction from patients in the intervention group, who are not able to expectorate, will be analyzed separately from the ITT analyses.

The primary analysis compares the tracheal suction group and the expiratory technique group to identify the most effective method for obtaining good quality sputum samples. The secondary analysis consists of an agreement analysis [48] between forced expiratory technique alone and forced expiratory technique after sputum induction.

Additionally, analysis of the secondary outcome of adverse effects will be conducted at baseline (right after allocation) and at the latest, 10 min. after the intervention. Clinical symptoms (cough, expectoration, chest pain, or dyspnea), SaO_2_, RR, and CR10 Borg scale [40] will be measured. Furthermore, a 5-point Likert scale will be used to measure patient experience of the procedure. The analyses will be adjusted for variables with a large influence on the outcome, which is an odds ratio larger than 2, to accommodate bias [49].

Descriptive analyses will be performed on the pathogens found when the specimens are cultured according to differential quality criteria.

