#### Analysis for primary outcome

For the primary outcome, the following analyses will be utilized:
To assess the suitability of the sputum sample between the two collecting methods groups, a hierarchical mixed effect logistic model with and without imputed values will be utilized to accommodate the random effect’s hierarchical structure, which manifests according to different personnel collecting the samples and geographical variation (Table 2).

**Table 2 Tab2:** Results of the primary outcome regarding specimens’ suitability and secondary outcome of adverse effects and patient experience. Tracheal suction method (reference group) compared to expiratory technique methods

Outcome	Unadjusted OR (CI) ***P***	Adjusted OR (CI) ***P***

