### Withdrawal from the study {24}

It is assumed that there will be minimal patient withdrawal from the study, as the specimens will be collected immediately after patient consent and allocation, and there will be no further patient contact. Withdrawals will be assumed to be missing completely at random (MCAR) [51].

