### Missing data {28+29}

Missing data includes patient withdrawals and sputum samples that are not possible to collect due to patients’ nonproductive cough or noncompliance. Multiple imputations and complete case analysis will be conducted to investigate the influence of missing data on the results [52]. The guidelines concerning missing data suggested by Sterne et al. will be followed to ensure transparency [53].

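### Specimens that cannot be obtained are set to missing, so the primary contrast leaves out the whole difference in obtaining a specimen and, on the plan's own rates, about 13% to 47% of the difference in good specimens per randomised patient

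*SAP article*

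**What the plan says.** Microscopy classifies a specimen with fewer than 10 squamous epithelial cells per field as suitable and adds: "The samples unable to be collected will be considered missing as the quality cannot be determined". Missing data {28+29} confirms this: "Missing data includes patient withdrawals and sputum samples that are not possible to collect", the stated reasons for non-collection being a nonproductive cough or noncompliance. It continues: "Multiple imputations and complete case analysis will be conducted to investigate the influence of missing data on the results". Analysis for primary outcome specifies that "a hierarchical mixed effect logistic model with and without imputed values will be utilized", without saying which of the two runs carries the conclusion.

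Patients in the intervention arm who cannot deliver a specimen go on to suction, and under Randomization {10} "these samples will not be included in the primary analyses". They reappear only in a descriptive sub-analysis that counts these suctions and their quality.

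Definition of analyses population {20} states: "The primary analysis will be conducted according to the intention-to-treat (ITT) principle". It defines that population as all consenting, allocated patients, and it gives the purpose of the primary analysis as finding which method is more effective for obtaining good specimens. Sample size consideration {11} assumes non-collection of 50% with forced expiration alone, 30% with induction added and 10% with suction.

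**The concern.** A nonproductive attempt is not an unobserved value. It is a known outcome of the method, and the plan expects it to occur more often in one arm.

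The complete-case run conditions on an event after randomisation, success in obtaining a specimen, so randomisation no longer protects the comparison. The imputed run keeps every patient but assigns a quality to specimens that never existed. Neither estimates how often a randomised patient ends up with a good specimen from the allocated method, and no between-arm comparison that counts failures is planned.

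At stake is the direction of error in a trial framed as non-inferiority. If the expiratory arm fails more often and its failures do not count against it, the comparison can look closer than it is.

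**Working it through.** **Inputs.** From Sample size consideration {11}: not obtained 10% (suction), 30% (induction plus forced expiration), 50% (forced expiration alone); good quality among obtained 90% (suction) and 75% (expiratory); 260 patients; power 84%. From Randomization {10}: 1:1 allocation, so 130 per arm. Significance level 0.05; its sidedness is not stated, so two-sided is assumed.

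The article does not give the failure rate for the combined expiratory arm. Two readings are used:
- A: 30% is the rate for the whole arm.
- B (assumption): induction is used only after failed forced expiration, and 30% applies to those patients, so 0.5 × 0.3 = 15%.

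The 50% figure is for forced expiration alone and is not used as an arm rate, because the arm offers both techniques.

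**Step 1: the plan's own power.** With failures dropped, suction has 130 × 0.90 = 117 analysed. The expiratory arm has 130 × 0.70 = 91 (A) or 130 × 0.85 = 110.5 (B). A difference test of 90% v 75% has power 81.7% (A) or 85.1% (B) by formula. Simulated fixed-effect logistic regression gives 82.0% to 82.6% (A) and 85.5% to 86.3% (B). The stated 84% lies between. It is therefore reproduced approximately as a test of difference among obtained specimens only. Random effects were not simulated because no variances are given.

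**Step 2: good specimens per randomised patient** = P(obtained) × P(good if obtained).

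| | Suction | Expiratory | Gap | Analysed | Left out |
|---|---|---|---|---|---|
| A | 0.90 × 0.90 = 81% | 0.70 × 0.75 = 52.5% | 28.5 points | 15 points | 13.5 of 28.5 = 47% |
| B | 81% | 0.85 × 0.75 = 63.75% | 17.25 points | 15 points | 2.25 of 17.25 = 13% |

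The difference in obtaining any specimen is 90% − 70% = 20 points (A) or 90% − 85% = 5 points (B). None of it enters the planned contrast.

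**Step 3: the imputed run.** If quality is imputed within arm from obtained specimens, the expected result is again about 90% v 75%. Imputation fills the empty cells but estimates the same conditional quantity.

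**Step 4: direction.** In percentage points, the part left out is (expiratory quality × expiratory failure rate) − (suction quality × suction failure rate). For A: 0.75 × 0.30 − 0.90 × 0.10 = 0.135. For B: 0.75 × 0.15 − 0.90 × 0.10 = 0.0225. Both are positive, so the planned contrast favours the expiratory arm.

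**Step 5: illustration for non-inferiority.** Assume a 15-point margin (the article calls 15 points a clinically significant difference, not a margin), one-sided 0.025, reading A, and equal quality of 75% among obtained specimens. The true per-patient deficit is 0.75 × (0.90 − 0.70) = 15 points. The complete-case standard error is √[0.75 × 0.25 × (1/117 + 1/91)] = 0.0605, so non-inferiority is declared with probability Φ(0.15/0.0605 − 1.96) ≈ 70%. Counting failures in all 130 per arm, it is 2.5%.

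**Step 6: power after the fix.** A two-sided difference test with 130 per arm has power 99.9% (81% v 52.5%) or 88% (81% v 63.75%).

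**The case against.** The best defence is that this is a choice of estimand. Hypothesis, aim, and objectives {8 +12} frames the aim and first objective as the quality of samples obtained by each method, and Outcome definitions {26} names sample quality as the primary outcome. Quality among obtained samples is a coherent reading of both. What remains is that it conflicts with the hypothesis, with the purpose stated in Definition of analyses population {20} and with the intention-to-treat label. Keeping fallback suction samples out of the intervention arm's successes is sound; the gap is that the failures behind them are not counted.

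A reader might go further in four ways that the documents do not support.

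- That most or all of the difference in good specimens is hidden. On the rates above the share is 13% to 47%. It is all hidden only if quality among obtained samples is equal, which the plan does not assume.
- That the analysis uses only patients in whom the method worked. This describes the complete-case run, not the imputed one.
- That interrupted procedures are assumed missing completely at random. Withdrawal from the study {24} applies that assumption to withdrawals. Harms {30} says "the procedure that is being performed will be interrupted preventing patient participation", which is ambiguous and does not class these patients as withdrawals.
- That a false non-inferiority claim is likely on the plan's own rates. At 90% v 75% the planned analysis has about 82% to 86% power to show a difference, so it would usually show the expiratory arm to be worse. The risk in Step 5 needs more similar quality than planned, and the margin there is borrowed.

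Scale also matters. Table 2 reports odds ratios. Expiratory against suction, the conditional odds ratio is 3/9 = 0.33; per randomised patient it is 0.26 (A) or 0.41 (B). The favourable bias therefore holds in percentage points under both readings, but on the odds-ratio scale only under A.

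**Conclusion.** The point holds in this form. Setting failed collections to missing, with no primary run named, contradicts the intention-to-treat label and the stated purpose of the primary analysis. Both planned runs leave out the whole difference in obtaining a specimen: 20 points if 30% is the arm's failure rate, 5 points under the assumed 15%. For good specimens per randomised patient, the planned contrast of 15 points stands against 28.5 or 17.25. In percentage points, the scale on which the plan states its clinically significant difference, the error favours the arm expected to fail more often and is anti-conservative for non-inferiority.

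The size rests on the plan's assumed rates and on how its 30% is read. Because the change alters what is estimated and could alter the conclusion, it should be settled before the analysis.

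**What to change.** Define the primary outcome as a good-quality specimen (fewer than 10 squamous cells per field) obtained by the allocated method, yes or no, in all randomised patients. Count no specimen, and a specimen obtained only by fallback suction, as no. Limit multiple imputation to specimens collected but without a result and to withdrawals. Name one run as primary. Report specimen obtained and quality among obtained specimens, each by arm, as supportive analyses. State whether 30% is the whole-arm failure rate, and restate the power.

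**Cost.** The composite mixes yield and quality, which is why both components should be shown. The change redefines the primary outcome after recruitment began, so it must be registered as an amendment with the trial registry and ethics committees, as the article's own section on adjustments before study start requires, and decided without sight of outcomes by arm. It should need no new measurements if failed attempts and fallback suctions are recorded, as the planned descriptive sub-analysis implies. If outcomes by arm have already been seen, report it as a labelled additional analysis beside the planned one.
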